|                                                                                                                                                               | WHO COVID 10 point ordinal severity scale level                                                                                                                                                             | Days 8, 29, 60                                 |
|                                                                                                                                                               | Overall survival                                                                                                                                                                                            | Up to and including day 60                     |
|                                                                                                                                                               | Inpatients only:
Viral clearance on or before d8 **                                                                                                                                               | Day 8                                          |
|                                                                                                                                                               | Inpatients only:
Duration of pyrexia in days (defined as a temperature $\geq 38^{\circ}\text{C}$ )                                                                                                | Up to and including day 60                     |
| Evaluate the safety and tolerability of favipiravir in the study population                                                                                   | Adverse events                                                                                                                                                                                              | Up to and including day 60                     |

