### **5.7.2 Adverse Reactions**

Adverse reactions have been noted in the US and Japanese clinical studies where lower doses and shorter durations of treatment were used than in this protocol. The most common reactions included increases in blood uric acid levels, nausea, vomiting, diarrhoea, headache, ALT&AST increases, UTI, decreases in neutrophil and white blood cell count and increases in blood triglycerides.

Further details can be found in the Investigator's Brochure.

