### **5.8 Dose Modifications for toxicity**

A subject should be removed from favipiravir treatment if one of the following criteria is met:

- AST or ALT > 5 x ULN
- ALT or AST > 3 x ULN AND total bilirubin > 2X ULN
- AST or ALT > 3 x ULN AND patient has right upper quadrant pain or eosinophilia
- Uric acid >20 mg/dL (1.2 mmol/l)
- Any other ≥ Grade 3 adverse event considered by the study team to be due to the trial drug.

Any > 3 x ULN AST or ALT event should be reported as a AE of Special Interest using the SAE form provided by the CRUK CTU Pharmacovigilance department.

No dose reductions are required for reductions in renal function if they occur during treatment. There no data for treatment with favipiravir during haemofiltration or dialysis – if this occurs during treatment the Sponsor & CI should be contacted to discuss the risk-benefit of continuing treatment for the individual case.

If remdesivir is administered in combination with favipiravir, EGFR must be >30ml/min and LFTs must be monitored daily during treatment with remdesivir. The stopping rules above for raised

transaminases apply for the combination treatment. Ensure remdesivir SmPC or equivalent source of information is consulted before initiating the combination treatment with favipiravir.

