#### **6.1.4 Reporting of a Serious Adverse Event**

Investigators must report all Serious Adverse Events (SAEs) to the Pharmacovigilance Office, CRUK CTU immediately and under no circumstances should this exceed 24 hours following first awareness of the event by the Investigator or site staff.

In addition, all incidences of AT (ALT or AST) elevation > 3 times upper limit of normal (ULN) are classed as adverse events of special interest and should be reported as SAEs within the timeframe stated above.

The following events are excluded from reporting as SAEs

- Elective hospitalisations
- Day case admissions for treatment of underlying disease
- A and E attendance for an event that is not immediately life threatening and does not result in admission

Serious Adverse Events occurring in the period between consent and randomisation do not require to be reported if they are unrelated to any study specific screening procedure.

SAEs can be reported via the following means:

Pharmacovigilance [contact]

Email: [[contact]](mailto:[contact])

For any guidance on SAE reporting please contact the Pharmacovigilance team on the following numbers:

[contact] or [name]

The purpose of this obligation is to ensure the CI on behalf of the Sponsor, has the necessary information to continuously assess the benefit-risk balance of the clinical trial.

For guidance on submitting and completing the initial and follow up SAE report forms please refer to the SAE report form Completion Guidelines, which will be provided by the Pharmacovigilance Office, CRUK CTU, Glasgow.

The CI will receive notification, by email, of all SAEs received.

SAEs must be reported locally by the PI at each site in accordance with the local practice at their site (i.e. R&D Office).

A follow-up report must be submitted when the SAE resolves, is unlikely to change, or as soon as additional information becomes available. If the SAE is a potential SUSAR then follow up information must be provided as quickly as possible and in the timeframe requested by the CRUK CTU and CI. All follow-up information is required to be reported promptly and follow up reports submitted until all AEs listed on the initial SAE report resolve. A follow-up report must be submitted if additional AEs listed on the initial SAE report have resolved or will never resolve. A follow-up report should also be submitted if additional AEs occur or new information becomes available about previously reported AEs.

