| Hospitalized; Mild disease |  | Hospitalized oxygen by NIV or High flow                                              | 13% | 9.6%  |
|                            |  | Hospitalized on supplemental oxygen                                                  | 13% | 11.3% |
|                            |  | Hospitalized not on supplemental oxygen                                              | 12% | 12.3% |
| Ambulatory                 |  | Symptomatic – assistance needed                                                      | 2%  | 2.3%  |
|                            |  | Symptomatic – independent                                                            | 16% | 21.8% |
|                            |  | Asymptomatic – viral DNA detected                                                    | 16% | 27.0% |

\*Abstracted from figure 6 in ISARIC COVID-19 Report: 02 April 2020

To detect this magnitude of difference with 90% power at the 5% 2-sided level of statistical significance requires 302 patients (151 per arm). This allows for the possibility of early stopping at two interim analyses after primary outcome data is available for 128 and 202 patients. The interim analyses are detailed in 7.3.

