#### **7.1.5 Safety**

The worst toxicity grades (including AEs of special interest) experienced during active treatment will be compared between the study arms using the Mann-Whitney U test. P-values will be interpreted in the context of the multiple tests performed. This analysis will be restricted to events that occur in more than 10% of patients in either arm.

All Serious Adverse Events (including SARs and SUSARs) will be tabulated.

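### The 10% frequency filter in section 7.1.5 can remove the one pre-specified AE of special interest, and uncommon severe or serious event terms, from the only planned between-arm safety comparison

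*Protocol*

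**What the plan says.** Table 1 makes safety a secondary objective ("Evaluate the safety and tolerability of favipiravir in the study population"), with adverse events up to day 60 as its endpoint.

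Section 7.1.5 sets out the analysis. "The worst toxicity grades (including AEs of special interest) experienced during active treatment will be compared between the study arms", using the Mann-Whitney U test, with p-values to be read in light of the number of tests. It then limits that comparison: "This analysis will be restricted to events that occur in more than 10% of patients in either arm". Serious events get a separate sentence: "All Serious Adverse Events (including SARs and SUSARs) will be tabulated". That sentence states no test, effect estimate or layout by arm.

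The event of special interest is defined in two other places. Section 5.8 says "Any > 3 x ULN AST or ALT event should be reported as a AE of Special Interest using the SAE form". Section 6.1.4 says that ALT or AST elevations above 3 x ULN "are classed as adverse events of special interest and should be reported as SAEs within the timeframe stated above". No other AE of special interest is named. Section 5.7.2 includes transaminase rises in its list of the most common reactions ("nausea, vomiting, diarrhoea, headache, ALT&AST increases, UTI"). It gives no rates and notes that the earlier studies used lower doses and shorter courses.

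**The concern.** Two adjacent statements in section 7.1.5 pull against each other. One brings the AE of special interest into the comparison because it matters in advance. The other lets it out again on frequency alone, whatever its severity or the size of the difference between arms.

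A frequency floor is a sensible guard against dozens of tests on minor AE terms. It does not suit a harm singled out beforehand, which deserves an estimate whether it is common or not. At stake is whether the final analysis gives a between-arm estimate of a liver signal, or of an uncommon severe reaction, that the trial is large enough to detect. This is a rule the protocol states, not a detail left open for the SAP.

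**Working it through.** **Arm size.** Section 7.1 gives 302 patients, 151 per arm, for 90% power at two-sided 5% and an odds ratio of 1.95. To check it, take the proportional-odds formula N = 12(z₁ + z₂)² / [ln(OR)² (1 − Σp̄³)], where p̄ is the mean category probability over the two arms. With (1.960 + 1.282)² = 10.51, ln(1.95)² = 0.446 and 1 − Σp̄³ = 0.978 from the protocol's control distribution, N = 289 for a design without interim looks. Simulating looks at 128, 202 and 302 patients with the boundaries in section 7.2 gives 90.2% power at 302 when the lower boundary is followed. So 151 per arm reproduces and is used below.

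**Threshold.** 10% of 151 is 15.1. Since 15/151 = 9.93% and 16/151 = 10.6%, an event must occur in at least 16 patients of one arm to be compared.

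**Splits that the filter drops** (151 per arm, two-sided Fisher exact test, Wald interval for the risk difference):

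| Patients with event | Rates | Risk difference (95% CI), points | Fisher p |
|---|---|---|---|
| 15 v 1 | 9.9% v 0.7% | 9.3 (4.3 to 14.2) | 0.0004 |
| 14 v 3 | 9.3% v 2.0% | 7.3 (2.2 to 12.4) | 0.010 |
| 12 v 1 | 7.9% v 0.7% | 7.3 (2.8 to 11.8) | 0.003 |
| 6 v 0 | 4.0% v 0% | 4.0 (0.9 to 7.1) | 0.030 |
| 15 v 6 | 9.9% v 4.0% | 6.0 (0.3 to 11.7) | 0.068 |
| 10 v 3 | 6.6% v 2.0% | 4.6 (0.1 to 9.2) | 0.085 |

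The last two rows show that not every dropped split is a clear difference. With 15 events in one arm, p stays below 0.05 for up to 5 in the other (15 v 5, p = 0.035).

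**How often the filter would bite.** The protocol gives no event rates, so the true rates here are assumptions. The probability of exclusion is P(X ≤ 15) in one arm times P(X ≤ 15) in the other, with X binomial on 151.

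| Assumed true rates | Probability dropped | Power of Fisher test without the filter |
|---|---|---|
| 5% v 1% | 0.996 | 0.40 |
| 6% v 0% | 0.98 | 0.90 |
| 8% v 1% | 0.85 | 0.82 |
| 10% v 2% | 0.56 | 0.81 |

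At 15% v 3% the probability falls to 0.05. The filter therefore matters for event rates up to roughly 10%.

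**Denominator.** The comparison covers active treatment, which ends on day 10. The outpatient schedule of events shows routine bloods at screening and next at day 15, whereas the inpatient schedule has them on days 1, 3 and 8. The 10% is nevertheless taken over all patients in the arm. If 75%, 50% or 33% of an arm were tested during dosing (assumed shares), 16 events would be 16/113 = 14%, 16/76 = 21% or 16/50 = 32% of those tested.

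**The case against.** A reader might infer that the hepatic event and other serious harms would never be compared between arms, or would go unseen. The documents do not support that.

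- **Visibility.** Every ALT or AST value above 3 x ULN must be reported as an SAE (section 6.1.4), and all SAEs are tabulated with no frequency floor (section 7.1.5). The data monitoring committee also reviews accruing unblinded data for safety (section 10.6). What is missing is a planned estimate or test in the final analysis.
- **The gravest outcomes are compared elsewhere.** Section 7.1.3 analyses level 7 or above or death by day 29, and survival over 60 days, by logistic regression with study arm. The day 15 primary model covers hospitalisation, ventilation and death.
- **SAEs taken together may well pass 10%.** Section 7.1 assumes 11% of controls dead and a further 5 + 7 + 5 = 17% in the ventilation categories at day 15. An overall any-SAE test would largely repeat the efficacy analysis, so the point concerns individual event terms.
- **The filter can be read another way.** Worst-grade comparisons usually run on graded terms. If the 10% is counted on ALT or AST increase of any grade, the term could pass, and its severe grades would then be compared. Section 5.7.2 makes that plausible, and section 7.1.5 does not say which count is meant.
- **Much of the remedy's detail is SAP material.** Choice of test, interval and table layout can properly sit there.

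All of these stand as limits on the point. None removes it: whether a harm named in advance gets a between-arm estimate should not depend on how terms are grouped, and the restriction itself is written in the protocol.

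**Conclusion.** The concern holds in a limited form and is worth correcting. Section 7.1.5 includes AEs of special interest in its between-arm comparison and then applies a 10% floor without exempting them. If the floor is applied to the event itself, ALT or AST above 3 x ULN and uncommon grade 3+ or serious event terms can drop out of the only planned between-arm safety comparison with up to 15 events in an arm, including splits as clear as 15 v 1. Those that are SAEs are then left to a tabulation without an estimate; a non-serious grade 3+ term does not have even that.

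This rests on 151 patients per arm and on counting the event rather than the any-grade term. The splits and true rates above are illustrations, since the protocol gives no expected rates, and the tested shares are assumed. The point does not extend to death or level 7 and above.

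**What to change.** In section 7.1.5, state that the 10% restriction does not apply to AEs of special interest or to grade 3+ and serious event terms. Report these by arm as the number of patients with the event, with a risk difference and 95% CI, adding Fisher's exact test for the AE of special interest. For this laboratory-defined event, take patients with a post-baseline liver test as the denominator. Keep the 10% filter for all other AE terms.

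The cost is one or two sentences and a few more safety comparisons, which section 7.1.5 already says are to be read in the context of multiple testing. Some serious COVID-19 events will overlap with the efficacy endpoints, and the report should say so. The change does not alter how many patients have liver tests during dosing; the tested denominator only makes that number visible.

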#### **7.2 Interim Analysis**

The stopping rules for the interim analyses are based on group sequential asymmetric boundaries using Hwang-Shih-DeCani spending functions with  $\gamma = -2.6$  (lower boundary) and  $\gamma = -9.5$  (upper boundary). The upper boundary is binding for early stopping; the lower boundary is non-binding and the Data Monitoring Committee may take into account the effect on secondary end-points in reaching their decision on whether the study should proceed or not.

| Analysis | N | Lower boundary |           |            | Upper boundary |           |              |
|----------|---|----------------|-----------|------------|----------------|-----------|--------------|
|          |   | Z              | Nominal p | Beta-Spend | Z              | Nominal p | Alpha -Spend |

|              |     |      |        |               |      |        |               |
|--------------|-----|------|--------|---------------|------|--------|---------------|
| Interim 1    | 128 | 0.00 | 0.5020 | 0.0160        | 3.72 | 0.0001 | 0.0001        |
| Interim 2    | 202 | 0.84 | 0.7992 | 0.0218        | 3.08 | 0.0010 | 0.0010        |
| Final        | 302 | 1.96 | 0.9751 | 0.0622        | 1.96 | 0.0249 | 0.0239        |
| Total |     |      |        | 0.1000 |      |        | 0.0250 |

At the first interim analyses the distribution of the primary end-point in the control arm will be reviewed by the Trials Steering Committee (TSC) to determine how well it conforms to the initial assumptions and whether or not any modifications may be required to the sample size calculations. This review is required because of limited experience with the primary end-point in this patient population. The TSC has no access to outcome data on the experimental arm.

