## 7 STATISTICS AND DATA ANALYSIS

### 7.1 Trial Design and Sample Size

The study is designed as an open-label randomised (1:1) phase II/III study which allows for early stopping for lack of efficacy or clear superiority in the experimental arm.

The study is powered to detect an improvement corresponding to an odds ratio of 1.95 in the cumulative odds of the WHO COVID 10-point ordinal severity scale assessed at day 15. This is equivalent to the probability of a patient having a better outcome at this time if allocated to experimental as compared to control of 66% (50% under null hypothesis). The following table illustrates that improvement:-

|                              | WHO COVID 10-point ordinal severity scale                                                                                | Assumed percentages on control arm at day 15* | Percentages on experimental arm at day 15 with odds ratio=1.95 |
|------------------------------|--------------------------------------------------------------------------------------------------------------------------|-----------------------------------------------|----------------------------------------------------------------|
| Death                        | Death                                                                                                                    | 11%                                           | 6.0%                                                           |
| Hospitalized; severe disease | Mechanical ventilation pO 2 /FIO 2 <150 and vasopressors, dialysis or ECMO                         | 5%                                            | 2.9%                                                           |
|                              | Mechanical ventilation pO 2 /FIO 2 >150 ( SpO 2 /FIO 2 >200) or vasopressors | 7%                                            | 4.4%                                                           |

|                            |  |                                                                                      |     |       |
|----------------------------|--|--------------------------------------------------------------------------------------|-----|-------|
|                            |  | ICU - intubation & mechanical ventilation, $pO_2/FIO_2 > 150$ or $SpO_2/FIO_2 > 200$ | 5%  | 3.3%  |

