#### **10.5 COVID-19 Umbrella Trial Steering Committee (COVID-19 UTSC)**

The role of the COVID-19 UTSC is to provide overall supervision of the trial and ensure that it is being conducted in accordance with the principles of GCP and the relevant regulations. The TSC should agree any significant protocol amendments, provide advice to the investigators on all aspects of the trial and have members who are independent of the investigators, in particular an independent chairperson. Decisions about continuation or termination of the trial or substantial amendments to the protocol are usually the responsibility of the TSC.

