#### **10.6 COVID-19 Umbrella Independent Data Monitoring Committee (COVID-19 UIDMC)**

The role of the COVID-19 UIDMC is to review the accruing trial data and to assess whether they are any safety or efficacy issues that should be brought to participants' attention or any reasons for the trial not to continue. In particular they will review the data at the prespecified interim analyses. The IDMC will be independent of both the investigators and will be the only body that may have access to unblinded data during the course of the trial. It will make recommendations to the TSC.

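### Section 7.2 shows the steering committee control-arm primary outcomes at interim 1 for a sample-size review with no stated rule, while Section 10.6 reserves unblinded data to the IDMC

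*Protocol*

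**What the plan says.** Section 7.2 of the protocol adds a separate review to the first interim analysis (128 patients with primary outcome data): "At the first interim analyses the distribution of the primary end-point in the control arm will be reviewed by the Trials Steering Committee (TSC"). The committee is to compare that distribution with the design assumptions and decide "whether or not any modifications may be required to the sample size calculations". The reason given is limited experience with this endpoint in this population. The section closes with a limit: "The TSC has no access to outcome data on the experimental arm". It gives no rule for turning what is seen into a new sample size.

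Section 10.6 says of the IDMC that it "will be the only body that may have access to unblinded data during the course of the trial", and that it advises the TSC. Section 10.5 describes the TSC's authority: "Decisions about continuation or termination of the trial or substantial amendments to the protocol are usually the responsibility of the TSC". It asks for members independent of the investigators, including the chair.

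Section 7.1 describes an "open-label randomised (1:1) phase II/III study" and states: "To detect this magnitude of difference with 90% power at the 5% 2-sided level of statistical significance requires 302 patients (151 per arm").

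**The concern.** Treatment is open-label, so clinicians know each patient's allocation. The only information that can still be withheld is the accumulating outcome summarised by arm. That is the sensible meaning of unblinded data in Section 10.6, and a control-arm distribution on the primary scale is such a summary. Section 7.2 gives it to a second body, so both statements cannot stand.

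The choice of body matters. The TSC receives the IDMC's advice, usually decides on amendments and continuation, and at this same look judges the sample size. A treatment comparison is a difference between two arms, so seeing one of them tells the viewer something about the difference. An unexpectedly poor control arm makes a favourable interim comparison more likely. If the sample size can then be changed at discretion, it can no longer be shown that the change was unrelated to the emerging effect. The error control of the group-sequential design assumes that it was.

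**Working it through.** **Reproducing the plan's figure.** Inputs from Section 7.1: control percentages, worst to best, 11, 5, 7, 5, 13, 13, 12, 2, 16, 16; odds ratio 1.95; 90% power; two-sided 5%.

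The proportional-odds formula for the total is N = 12(1.96 + 1.2816)² / [(ln 1.95)² (1 − Σp³)], where p is each category's proportion *averaged over both arms*.

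- (1.96 + 1.2816)² = 10.507 and (ln 1.95)² = 0.446, so N = 282.7 / (1 − Σp³).
- Applying 1.95 to the control column gives an experimental column of 6.0, 2.9, 4.4, 3.3, 9.6, 11.3, 12.3, 2.3, 20.8, 27.1.
- The averages give Σp³ = 0.0222 and N = 282.7 / 0.9778 = 289.
- The stated boundaries inflate this by 1.039, to 300.5, against 302 in the protocol. The design figure is reproduced to within two patients.

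**The printed experimental column.** It sums to 100.9%. For score 2 (symptomatic, independent), the control cumulative percentages from the worst end are 68% before the row and 84% after it. Dividing the odds by 1.95:

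- 0.84/0.16 = 5.25; 5.25/1.95 = 2.692; probability 0.729.
- 0.68/0.32 = 2.125; 2.125/1.95 = 1.090; probability 0.522.
- The difference is about 20.8%, where the table prints 21.8%. N is still about 289 with the printed value, but the column should not serve as a benchmark uncorrected.

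**Is the control result independent of the effect?** Take 64 patients per arm at interim 1 and a normal approximation, with C and E the standardised control and experimental results, so that Z₁ = (E − C)/√2. With no treatment effect:

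- correlation of C with Z₁ = −1/√2 = −0.71;
- correlation of the pooled result (E + C)/√2 with Z₁ = (1 − 1)/2 = 0.

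Control-arm data therefore carry information about the interim effect. Pooled data do not, under the null hypothesis.

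**How much could it matter?** Suppose the final total N is chosen after seeing C = c, there is no interim stopping, and the final test uses an unadjusted 1.96. Given c, the final statistic has mean −√(128/N)·c/√2 and variance 1 − 128/(2N). The chance of a false positive is the upper normal tail beyond [1.96 + √(128/N)·c/√2] / √(1 − 128/(2N)). The worst case picks, for every c, the N that maximises this, and then averages over c. With N fixed at 302 it returns 0.025, as it should. The protocol sets no limits on N, so the ranges below are assumptions:

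| Range allowed for final N | Worst-case one-sided error |
|---|---|
| 302 to 604 | 0.028 |
| 202 to 604 | 0.031 |
| 151 to 604 | 0.034 |
| 128 to 604 | 0.036 |

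**What would reveal the experimental arm?** Under 1:1 allocation, experimental = 2 × pooled − control. With the design death rates, pooled = (11 + 6.0)/2 = 8.5%, and 2 × 8.5 − 11 = 6.0%. Both quantities are needed. Section 7.2 supplies only the control one.

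**The case against.** A single prespecified look at the control arm alone is a recognised choice. The protocol gives its reason and states an access limit, and the committee must have an independent chair. A control-arm look also tests the design assumption directly, whereas a pooled look mixes a wrong control assumption with the treatment effect. All of that stands, and it means the TSC review is not improper in itself. It does not remove the conflict: if the look is intended, Section 10.6 is wrong as written.

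The error figures are also open to challenge. They are a ceiling for each range, reached only by a decision-maker who optimises against the true null distribution. A change driven strictly by the formula would do little, because N = 282.7 / (1 − Σp³) moves slowly: even the control column put in directly gives 287. This stands too. The exposure comes from discretion without a rule, not from re-estimation as such.

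A reader might infer that the TSC can obtain the experimental-arm results by subtraction. The documents do not support that. Nothing gives the TSC pooled day-15 outcomes. Section 6.1.4 says "The CI will receive notification, by email, of all SAEs received", but that is the chief investigator, and no text routes the totals to the TSC. SAEs also run to day 60 and cover everyone enrolled, so they do not match day-15 status in the first 128 patients. Minimisation with a random component does not guarantee exactly 64 per arm. Equally, nothing bars overall outcome or death counts from reaching the TSC, so subtraction remains a conditional risk.

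**Conclusion.** The conflict between Sections 7.2 and 10.6 is real and needs reconciling. It should be corrected before the first interim analysis, because the body shown one arm's outcomes is also the body that judges the sample size and usually decides amendments, and no rule constrains that judgement.

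The control-arm result and the interim effect correlate at about −0.71. The worst-case one-sided error is about 0.028 to 0.036 instead of 0.025. This rests on equal arms, a normal approximation, no interim stopping, an unadjusted final test, the assumed limits on N and an optimising decision-maker. Realistic inflation would be smaller. The more likely damage is to credibility: a change made at 128 patients could not be shown to be independent of the effect.

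The evidence does not extend to saying that the TSC knows, or can work out, the experimental-arm results. That would need overall counts that the protocol does not provide to it.

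**What to change.** In Section 7.2, base the TSC's sample-size review on the primary-endpoint distribution pooled over both arms. Compare it with the average of the control column and the experimental column recalculated at an odds ratio of 1.95: 8.5, 3.95, 5.7, 4.15, 11.3, 12.15, 12.15, 2.15, 18.4 and 21.55%, worst to best. State that any change to N follows from putting the pooled proportions into the proportional-odds formula. Keep every by-arm distribution, control alone included, with the IDMC, so that 7.2 agrees with 10.6 and the pooled figures cannot be differenced. In the Section 7.1 table, correct the score 2 row to about 20.8%.

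The cost is about a paragraph of wording and one table entry. No boundary changes, and 302 stands. Section 7.1.1 already allows a blinded assessment for a different decision, so the approach fits the protocol. The downside is that the control assumption is checked only indirectly: a pooled distribution that departs from the benchmark may reflect either the control rates or the treatment effect. If a direct check is wanted, the IDMC can make it and pass on only a sample-size recommendation.
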